# Goals

- 1. Primary goals
  2. Phase I: To determine the maximum tolerated dose of ibrutinib in combination with pembrolizumab in patients with advanced melanoma.
  3. Dose Expansion Cohort: To estimate the overall response rate treated at the maximum tolerated dose of ibrutinib in combination with pembrolizumab in patients with advanced melanoma.
  4. Secondary goals
  5. To assess the safety and adverse-event profiles of combination of ibrutinib with pembrolizumab in patients with advanced melanoma.
  6. To evaluate the overall response rate (ORR) in patients with advanced melanoma receiving ibrutinib and pembrolizumab.
  7. To evaluate the duration of response, progression-free survival (PFS), and overall survival (OS) in patients with advanced melanoma receiving ibrutinib and pembrolizumab.
  8. To assess the effect of treatment with ibrutinib and pembrolizumab on Th1/Th2 immune polarity.
  9. Exploratory goals
  10. To assess the CD8 T cell response to multiple melanoma-associated antigens, and to correlate CD8 T cell responses with changes in Th1/Th2 immune polarity
  11. To assess changes in plasma cytokines induced by treatment with ibrutinib and pembrolizumab
  12. To assess the change in potential biomarkers, such as tumor-bound and soluble PD-L1 levels and tumor-infiltrating lymphocytes, that may correlate with treatment responses.

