# Test Schedule

| Treatment Cycle | Pre- registration | ≤14 days prior to  regist- ration | Active Monitoring Phase | | | | | |
| --- | --- | --- | --- | --- | --- | --- | --- | --- |
|  |  |  | Cycles 1-4^1^ | | | | Day 1 Subsequent cycles [21- day cycle] | At confirmed disease progression^2^ |
| Tests and procedures |  |  | C1D8 (±1  day) | C2D1 (±3  days) | C3D1 (±3  days) | C4D1 (±3  days) | (± 3 days) |  |
| HLA Class I Typing^R^ |  | X |  |  |  |  |  |  |
| ECOG performance status |  | X | X | X | X | X | X | X |
| History, physical exam, vital signs^3^, and weight |  | X | X | X | X | X | X | X |
| Child Pugh Score |  | X |  | X | X | X | X | X |
| Height |  | X |  |  |  |  |  |  |
| Adverse event assessment |  | X | X | X | X | X | X | X |
| Urine Pregnancy test |  | X4 |  |  |  |  |  |  |
| CBC with Differential:^5^ |  | X6 | X | X | X | X | X | X |
| Chemistry group: AST, ALT,  Bilirubin (total and direct), Creatinine, albumin, INR, LDH |  | X6 | X | X | X | X | X | X |
| TSH |  | X7 |  |  | X |  | X7 | X |
| Tumor imaging and measurement ^,8^ |  | X8 |  |  |  |  | X9 | X |
| Research blood specimens (see Section 14.0)^10,R^ |  | X | X | X | X | X | X10 | X |
| Tissue specimens (see Section 17.0)^,R^ | X11 |  |  |  |  |  | X12 | X12 |
| BRAF V600E and V600K  mutation testing |  | X |  |  |  |  |  |  |

- - 1. Cycle 1= 28 day, Subsequent Cycles=21 days.
    2. Confirmed progression is an objective status of progression on two consecutive evaluations at least 6 weeks apart.
    3. Vital signs must include blood pressure and heart rate.
    4. For women of childbearing potential only. Must be done ≤7 days prior to registration.
    5. CBC differential must include hemoglobin, platelets, absolute neutrophil count, absolute lymphocyte count, and absolute monocyte count
    6. CBC with differential and chemistry groups must be done ≤14 days prior to registration.
    7. TSH testing is to be performed ≤14 days prior to registration. And at the end of each even numbered cycle ( 2, 4, 6, 8, 10, etc.) until confirmed progression. If TSH is abnormal, T3 and free T4 testing should be performed.
    8. The initial tumor imaging (either CT or MRI, with preference for CT) will be performed ≤28 days prior to registration. The same imaging technique will be used in a patient throughout the study. If an excisional biopsy of a target lesion is to be done, baseline tumor imaging must be performed after the biopsy is done.

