    9. Imaging is to be performed at the end of Cycle 4, 6, 8, 10, and 12. If a patient has not had a confirmed disease progression after Cycle 12, subsequent scans will take place at the end of every 3^rd^ cycle of treatment thereafter (that is, at the end of Cycle 15, 18, 21 until confirmed disease progression). See Section 11.
    10. Mandatory research blood specimen will be collected at Cycle 1 Day 8 and at the beginning of each cycle for Cycles 2-4, then at the beginning of every cycle when tumor imaging is performed until confirmed progression or at treatment discontinuation if not for PD.
    11. Mandatory core needle biopsy. A newly obtained tumor biopsy is required, unless tissue is

available for research use from a prior biopsy obtained ≤90 days prior to registration.

- - 1. Mandatory tissue/biopsy is required at the time of the first disease assessment (the evaluation at the end of Cycle 4). Optional tissue/biopsy will be obtained at the time of confirmed progression. Prior to and following biopsy hold ibrutinib per section 8.4.

R Research funded (see Section 19.0)

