# Treatment Evaluation Using RECIST Guideline

- 1. Requirements

The first scan after treatment initiation will be performed at the completion of Cycle 4 and will be then performed at the complete of every other cycle of treatment until disease progression is confirmed or 12 cycles of treatment have been administered without a confirmed disease progression (that is, imaging is to be done at the end of Cycles 4, 6, 8, 10, and 12). If a patient has not had disease progression after Cycle 12, subsequent scans will take place at the end of every 3^rd^ cycle of treatment thereafter (that is, at the end of Cycle 15, 18, 21 until confirmed disease progression)

Disease progression for this protocol is defined as meeting the RECIST criteria for disease progression on two consecutive evaluations at least 6 weeks apart.

- 1. Definitions of Measurable and Non-Measurable Disease
  2. Measurable Disease
  3. A non-nodal lesion is considered measurable if its longest diameter can be accurately measured as ≥1.0 cm with CT scan, CT component of a PET/CT, or MRI.
  4. A malignant lymph node is considered measurable if its short axis is

>1.5 cm when assessed by CT scan (CT scan slice thickness recommended to be no greater than 5 mm).

**NOTE:** *Tumor lesions in a previously irradiated area are not considered measurable disease.*

- 1. Non-Measurable Disease

All other lesions (or sites of disease) are considered non-measurable disease, including pathological nodes (those with a short axis ≥1.0 to <1.5 cm). Bone lesions, leptomeningeal disease, ascites, pleural/pericardial effusions, lymphangitis cutis/pulmonis, inflammatory breast disease, and abdominal masses (not followed by CT or MRI), are considered as non-measurable as well.

**NOTE:** ‘Cystic lesions’ thought to represent cystic metastases can be considered as measurable lesions, if they meet the definition of measurability described above. However, if non-cystic lesions are present in the same patient, these are preferred for selection as target lesions.

Lymph nodes that have a short axis <1.0 cm are considered non- pathological (i.e., normal) and should not be recorded or followed.

- 1. Guidelines for Evaluation of Measurable Disease
  2. Measurement Methods:
- All measurements should be recorded in metric notation (i.e., decimal fractions of centimeters) using a ruler or calipers.

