     2. If the positive FDG-PET at follow-up is not confirmed as a new site of disease on CT at the same evaluation, additional follow-up CT scans (i.e., additional follow-up scans at least 4 weeks later) are needed to determine if there is truly progression occurring at that site. In this situation, the date of PD will be the date of the initial abnormal PDG-PET scan.

iii If the positive FDG-PET at follow-up corresponds to a pre-existing site of disease on CT that is not progressing on the basis of the anatomic images, it is not classified as PD.

- 1. Measurement at Follow-up Evaluation:
     - A subsequent scan must be obtained 6 weeks following initial documentation of an objective status of either complete response (CR) or partial response (PR).
     - In the case of stable disease (SD), follow-up measurements must have met the SD criteria at least once after study entry at a minimum interval of

6 weeks until Cycle 12, thereafter every 12 weeks (see Section 11.44).

- - - The cytological confirmation of the neoplastic origin of any effusion that appears or worsens during treatment when the measurable tumor has met criteria for response or stable disease is mandatory to differentiate between response or stable disease (an effusion may be a side effect of the treatment) and progressive disease.
    - Cytologic and histologic techniques can be used to differentiate between PR and CR in rare cases (e.g., residual lesions in tumor types such as germ cell tumors, where known residual benign tumors can remain.)
  1. Measurement of Effect
  2. Target Lesions & Target Lymph Nodes
- Measurable lesions (as defined in Section 11.21) up to a maximum of 5 lesions, representative of all involved organs, should be identified as “Target Lesions” and recorded and measured at baseline. These lesions can be non- nodal or nodal (as defined in 11.21), where no more than 2 lesions are from the same organ and no more than 2 malignant nodal lesions are selected.

**Note:** If fewer than 5 target lesions and target lymph nodes are identified (as there often will be), there is no reason to perform additional studies beyond those specified in the protocol to discover new lesions.

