# Treatment/Follow–up Decision at Evaluation of Patient

- 1. Continuation of therapy

Patients who have not had disease progression and have experienced acceptable toxicity are to continue treatment per protocol until confirmed PD, unacceptable toxicity or refusal. And then they will go to event monitoring where patient and disease status will be reported every 6 months until death or a maximum of 5 years post-registration.

- 1. Progressive disease

The first instance in which a patient’s disease status meets the RECIST criteria for PD will continue two additional cycles of treatment per protocol and then undergo disease revaluation. If the initial documented progression is not confirmed by this scan, patients will continue treatment per protocol. If the initial documented progression is confirmed by this scan, patients will go to the event-monitoring phase where patient and disease status will be reported every 6 months until death or a maximum of 5 years post- registration. ***Exception: Patients who develop PD in the CNS should discontinue study treatment and go to Event Monitoring.***

- 1. For those on treatment at least one year and in complete response (CR)

At investigator’s discretion patients who have completed at least one year of protocol therapy and have had a complete response (CR) may discontinue all protocol therapy when the duration of the complete response has been at least 6 months (that is, at least 3 consecutive scans showing CR).

- 1. Discontinuation of protocol therapy

Criteria for discontinuation of protocol therapy include:

- - - Disease progression: Where disease progression is: the development of a new metastatic lesion or an objective status of disease progression (as defined by RECIST criteria) on two consecutive evaluations at least 6 weeks apart (section 13.2). ***Exception: Patients who develop PD in the CNS should discontinue study treatment.***
    - Request by patient to discontinue study treatment
    - Unacceptable toxicity
    - Intercurrent illness that would, in the judgment of the investigator, affect assessments of clinical status to a significant degree or require discontinuation of drug
    - Administration of radiotherapy, non-protocol chemotherapy, immunotherapy, biological agents, or an experimental drug during the trial
    - Development of new primary cancer
    - Ineligibility

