    - Dose Expansion Cohort: The endpoint is tumor response. Patients will be classified with respect to their best tumor response during treatment (e.g., CR, PR, SD, confirmed PD, Death, Too Early, or Not Evaluable). Estimates of tumor response and binomial confidence intervals will be reported. A patient whose tumor has meet the RECIST criteria for CR or PR on two consecutive evaluations at least 8 weeks apart is considered to have had a tumor response.

Adverse events: The maximum grade of each type of toxicity will be recorded for each patient. For each toxicity reported by dose level, the percentage of patients developing any degree of that toxicity as well as the percentage of patients developing a severe degree (Grade 3 or higher) will be determined.

Secondary end points include tumor response (for the Phase I/Dose Seeking Cohort), progression-free survival (PFS) and overall survival (OS) time: A patient whose tumor has meet the RECIST criteria for CR or PR on two consecutive evaluations at least 8 weeks apart is considered to have had a tumor response. Survival time is defined as the time from study entry to death due to any cause. Progression-free survival time is the time from study entry to the documentation of disease progression. If a patient dies

without a recurrence documented, the patient will be considered to have progressed on their death date.

All the study observations pertaining to adverse events, MTD, response, time to event points and laboratory correlates will be examined in an exploratory and hypothesis- generating fashion. The small sample size and the heterogeneous patient population associated with Phase I studies restricts the generalizability of the results. Any notable statistical finding will be viewed as an impetus for further study in Phase II trials rather than a definitive finding in and of itself.

- 1. Monitoring of the trial

This clinical trial will be monitored by the Mayo Clinic Cancer Center Data and Safety Monitoring Board (MCCC DSMB). The study statistician will prepare a report containing accrual and adverse event that will be submitted to MCCC DSMB every 3 months.

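### The primary endpoint limits best response to the treatment period, so, as written, a CR or PR confirmed only after both drugs stop for toxicity does not count

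*Protocol*

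**What the plan says.** Four provisions of the protocol act together.

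- **Window and confirmation.** Section 16.6, for the dose expansion cohort: "Patients will be classified with respect to their best tumor response during treatment". A later sentence in the same paragraph says that a patient meeting the RECIST criteria for CR or PR "on two consecutive evaluations at least 8 weeks apart is considered to have had a tumor response".
- **Scan timing.** Test Schedule, Section 4.0: "Imaging is to be performed at the end of Cycle 4, 6, 8, 10, and 12". Section 11.1 adds that "subsequent scans will take place at the end of every 3^rd^ cycle of treatment thereafter". Cycle lengths are given as "Cycle 1= 28 day, Subsequent Cycles=21 days". Section 11.33 also says: "A subsequent scan must be obtained 6 weeks following initial documentation of an objective status", meaning a first CR or PR.
- **Leaving treatment.** Table 8.2 takes patients off both drugs and into Event Monitoring for several toxicities. Examples are Grade 3 hepatic dysfunction, Grade 3 or higher pneumonitis, acute kidney injury and infusion reaction, and most other immune-related events of Grade 3 or higher. On patients who end treatment, Section 13.1 says: "And then they will go to event monitoring where patient and disease status will be reported every 6 months until death", up to 5 years after registration. The Test Schedule has no event-monitoring column.
- **Denominator and rule.** Section 16.6 analyses every eligible, consented patient who began treatment. Section 16.3 takes 2 responses in 14 such patients as a sign of promising activity.

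**The concern.** A response needs a second scan some weeks after the first, and the window closes when treatment stops. A patient in PR at the Cycle 4 scan who stops both drugs for a Table 8.2 toxicity in Cycle 5 has had no chance to be confirmed inside the window. If a later scan shows the response has held, the wording of Section 16.6 still leaves it out. The patient remains in the denominator because treatment was begun. Section 16.4 gives ineligibility and cancellation as its examples of non-evaluable patients, not stopping for toxicity.

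The loss is tied to toxicity, so it is not random, and it runs in one direction: the primary response rate is pulled down. With a threshold of 2 in 14, one reclassified patient can change the conclusion.

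The text can also be read the other way. Two analysts following it in good faith could classify the same patient differently on the primary endpoint.

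**Working it through.** **1. The plan's own figures.** Section 16.3 uses the binomial distribution with n = 14. At a true rate of 20%, P(0 responses) = 0.80^14 = 0.044, so P(at least 1) = 0.956, which matches the stated 95%. The cumulative values for 0 to 3 responses come out as 0.044, 0.198, 0.448 and 0.698 at 20%, and as 0.0068, 0.0475, 0.161 and 0.355 at 30%. Both sets agree with the tables within rounding. The design arithmetic is correct; the problem lies in what counts as a response.

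**2. When confirmation can occur.** Inputs are the cycle lengths and scan cycles in Sections 4.0 and 11.1. End of Cycle c = 28 + 21 × (c − 1) days.

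| Scan at end of Cycle | Day | Week | Gap from previous scan |
|---|---|---|---|
| 4 | 91 | 13 | – |
| 6 | 133 | 19 | 6 weeks |
| 8 | 175 | 25 | 6 weeks |
| 10 | 217 | 31 | 6 weeks |
| 12 | 259 | 37 | 6 weeks |
| 15 | 322 | 46 | 9 weeks |

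- Lenient reading (PR at Cycle 4 still present at Cycle 8): confirmed at week 25, which is 25 − 13 = 12 weeks after the first response.
- Literal reading (two consecutive scheduled scans at least 8 weeks apart): the first pair that qualifies is Cycles 12 and 15, so confirmation comes at week 46, which is 46 − 13 = 33 weeks after the first response. Visit windows of 3 days at each end stretch the 42-day gap only to 48 days, short of 56.
- The Section 11.33 scan, 6 weeks after the first response, also falls short of 8 weeks.

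A patient who responds at week 13 must therefore stay on treatment for a further 12 to 33 weeks to count on scheduled scans.

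**3. Effect on the 2-in-14 rule.** Let p be the true response rate and L the share of true responders who stop both drugs before confirmation. The protocol gives no L, so the values below are assumptions. The observed rate is e = p × (1 − L), and P(at least 2 of 14) = 1 − (1 − e)^14 − 14e(1 − e)^13.

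| p | L | e | P(at least 2 of 14) |
|---|---|---|---|
| 20% | 0 | 0.20 | 1 − 0.044 − 0.154 = 0.802 |
| 20% | 15% | 0.17 | 1 − 0.074 − 0.211 = 0.715 |
| 20% | 30% | 0.14 | 1 − 0.121 − 0.276 = 0.603 |
| 26% | 0 | 0.26 | 0.913 |
| 26% | 30% | 0.182 | 0.753 |

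The 26% is the pembrolizumab response rate cited in the Background. At p = 20% the expected number of counted responders falls from 14 × 0.20 = 2.8 to 14 × 0.14 = 1.96 when L = 30%.

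**The case against.** **The consequence is inferred.** No sentence says that such a patient is a non-responder. The on-treatment limit sits in the classification sentence and is not repeated in the sentence defining response. Section 11.33 does not confine its scan to patients on treatment, and Section 16.6 lists a Not Evaluable category. This stands as far as it goes: an off-treatment confirmation could be admitted. But then the primary endpoint has two readings, and calling the patient Not Evaluable does not remove the patient from the stated denominator.

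**The mechanism is narrow.** Many Table 8.2 events lead to a hold, and pembrolizumab may continue when only ibrutinib is stopped. Only patients who leave both drugs between first response and confirmation are affected. That is right, and it is why L cannot be read off the protocol.

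**The 20% may already be net of such losses.** If the rate in Section 16.3 means response exactly as Section 16.6 defines it, nothing should be deducted. That is a fair reading, but the 20% would then no longer describe the tumour activity of the combination.

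**The effect is conservative and the study exploratory.** There is one arm, results are declared hypothesis-generating, and treating unconfirmed responses as failures is a recognised choice. This limits the weight of the point. It does not justify setting aside a confirmation actually obtained.

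**A stronger reading that fails.** A reader might infer that PFS and duration of response are dated later once treatment stops, because follow-up moves to six-monthly status. The documents do not show this. Six months is a reporting interval, not a scan interval; PFS runs to documented progression, which can carry its own date; Section 18 asks for documentation of progression after study therapy and points to a data submission schedule that is not shown. Nor do patients who stop in CR under Section 13.3 bear on the primary endpoint: they need at least three consecutive scans showing CR and are already responders.

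**Conclusion.** The point holds as a defect in the wording of the primary endpoint. Taken literally, Section 16.6 excludes a confirmation obtained after both drugs stop, keeps the patient in the denominator and so lowers the response rate through toxicity. Taken leniently, it does not, and the protocol does not say which reading applies.

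At a true rate of 20%, the chance of meeting 2 in 14 falls from 80% to 72% if 15% of true responders are lost and to 60% if 30% are. These figures rest on the assumed loss, on the literal reading, and on taking 20% as the rate before such losses. They illustrate sensitivity and do not estimate what happened in the trial.

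The mismatch between the 8-week rule and 6-week scans makes the exposure longer and must be resolved with it. The change is worth making, in proportion to a small exploratory cohort.

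**What to change.** In Section 16.6:

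1. Replace the on-treatment window with assessment from registration until progression or the start of non-protocol anticancer therapy, whether or not study treatment continues.
2. State that a confirming scan obtained after treatment stops counts towards response.
3. Reconcile the 8-week confirmation interval with the 6-week scan in Section 11.33 and the 6-week spacing through Cycle 12, so that the scan the protocol already requires can confirm a response. Without this, the first two edits would not help a patient in PR at Cycle 4 who stops in Cycle 5, because the Section 11.33 scan would still come too early to confirm.

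The cost is mainly endpoint wording. No dose or treatment rule changes, Section 11.33 already requires the scan, and Section 19 lists tumour imaging as routine clinical care. If the sponsor prefers to keep 8 weeks, the required scan would have to be timed to match. The small downside is that some responses will be credited after dosing has ended.

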# Protocol Treatment

- 1. Treatment Schedule

Use actual weight or estimated dry weight if fluid retention Cycle 1 treatment = 28 days

All subsequent treatment cycles = 21 days (±3 days)

| Drug | Dose | Treatment | Retreatment |
| --- | --- | --- | --- |
| Ibrutinib | assigned at registration | PO daily (Day 1 to 28  of Cycle 1, then Day 1- 21* on subsequent cycles) | Every 21 days  (±3 days)  until confirmed progression |
| Pembrolizumab | 200 mg | IV injection on Day 8 of Cycle 1 and then Day 1 of each  subsequent cycle | Every 21 days (±3 days) until confirmed progression |

* Patients should receive a sufficient quantity of ibrutinib to last until the next scheduled treatment visit.

- 1. Determination of Maximum Tolerated Dose (MTD)
  2. Dose Escalation Scheme

| Dose level | Ibrutinib** |
| --- | --- |
| -1 | 140 mg |
| 0* | 280 mg |
| 1 | 420 mg |

* Starting dose level

** If the patient has clinical or laboratory evidence of liver failure during the treatment, then calculate the Child-Pugh score and adjust the ibrutinib dose (see Table 8.3).

NOTE: Doses will not be escalated in any individual patient.

- 1. MTD Determined

As of MCCC Amendment 6, the MTD has been determined to be Dose Level 1. Dose Level 1 will be used for the expansion cohort.

- 1. Dose Limiting Toxicities

Dose limiting toxicities (DLT) are defined to be:

| ***Toxicity*** | ***DLT Definition*** |
| --- | --- |
| Hematologic | Grade 4 ANC, Grade 4 Hgb, or PLT <25,000 |
| Renal | Serum creatinine ≥2 times baseline |
| Neurologic | ≥Grade 2 neurosensory or neuromotor toxicity |
| Other nonhematologic | ≥Grade 3 per NCI Common Terminology Criteria for Adverse Events (CTCAE) version 4.0* |

*Grade 3 rash or fever despite maximal supportive treatment(s) will be considered dose-limiting; all grade 4 rash and fever will be considered a DLT.

The maximum tolerated dose is defined as the highest dose level among those tested where at most one out of 6 patients develops a DLT prior to the start of their second cycle of treatment and the next highest dose level is such that 2 out of a maximum of 6 patients treated at this dose level developed a DLT prior to the start of their second cycle of treatment.

- 1. Dose escalation plan

NOTE: As of MCCC Amendment 6, the MTD has been determined to be Dose Level 1. A minimum of 2 or a maximum of 6 patients will be accrued to a given dose level.

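### The response definition needs two consecutive scans at least 8 weeks apart, but on-schedule scans through Cycle 12 are 6 weeks apart, so no such pair can confirm a response

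*Protocol*

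**What the plan says.** Protocol Section 16.6 makes tumor response the endpoint of the dose expansion cohort and credits it to "A patient whose tumor has meet the RECIST criteria for CR or PR on two consecutive evaluations at least 8 weeks apart". It repeats the rule for the secondary response endpoint of the dose-seeking cohort.

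The scan calendar is set elsewhere:

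- Section 4, Test Schedule, footnote 1: "Cycle 1= 28 day, Subsequent Cycles=21 days". Section 7.1 gives the later cycles a window of 3 days either way.
- Section 11.1: "imaging is to be done at the end of Cycles 4, 6, 8, 10, and 12". Section 4 gives the same list. After Cycle 12, scans come every third cycle, "at the end of Cycle 15, 18, 21 until confirmed disease progression".
- Section 11.33, for a first CR or PR: "A subsequent scan must be obtained 6 weeks following initial documentation of an objective status".

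Progression is confirmed at a minimum of 6 weeks (Sections 4, 11.1 and 13.4). Section 16.3 treats 2 responses in 14 patients as promising, and gives the short-term nature of the primary endpoint as one reason for choosing the Gehan design.

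**The concern.** The confirmation interval is longer than the gap between scans, so the follow-up scan that Section 11.33 orders cannot, on schedule, confirm a response under Section 16.6. Progression can be confirmed at the next scan; response cannot.

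What is at stake is the count of responders. The go signal is 2 of 14, so classifying one patient differently can reverse it. An endpoint that an on-schedule patient cannot meet for most of a year also sits badly with the description of it as short term.

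**Working it through.** **Design figures first.** The stated binomial figures reproduce. With n = 14 and p = 0.20, P(at least 1) = 1 − 0.8^14 = 0.956, against the stated 95%. P(at most 0, 1, 2, 3) = 0.044, 0.198, 0.448, 0.698, as tabulated. At p = 0.30 the values are 0.007, 0.047 (0.0475 before rounding), 0.161 and 0.355, also as tabulated. The sample-size arithmetic is not in question.

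**Scan calendar.** End of Cycle c = 28 + 21 × (c − 1) days.

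| Scan at end of cycle | Day | Week | Gap from previous scan |
| --- | --- | --- | --- |
| 4 | 91 | 13 | n/a |
| 6 | 133 | 19 | 42 days |
| 8 | 175 | 25 | 42 days |
| 10 | 217 | 31 | 42 days |
| 12 | 259 | 37 | 42 days |
| 15 | 322 | 46 | 63 days |
| 18 | 385 | 55 | 63 days |

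**Comparison with 8 weeks (56 days).**

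- Two-cycle gap with the cycle windows: 42 ± (2 × 3) = 36 to 48 days. A further 3-day slip at each end would give 48 + 6 = 54. Every value is below 56.
- Cycle 12 to Cycle 15: nominally 63 days, which qualifies and completes at week 46. With windows the range is 63 ± (3 × 3) = 54 to 72 days, so even this pair can fall short if all three cycles run early.
- Response first seen at Cycle 12: Section 11.33 adds a scan at day 259 + 42 = 301 (week 43). Cycles 12 and 15 are then no longer consecutive. The gaps are 42 days and 322 − 301 = 21 days, so the first qualifying pair is Cycle 15 to Cycle 18, completing at week 55.

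**One patient, three rules.** Take PR or CR on the Cycle 4, 6, 8 and 10 scans, all on schedule, then progression or stopping.

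| Rule | Classification |
| --- | --- |
| Section 16.6 read literally | Non-responder |
| Response sustained over consecutive scans spanning at least 8 weeks | Responder at Cycle 8 (175 − 91 = 84 days; week 25) |
| Confirmation at the 6-week scan of Section 11.33 | Responder at Cycle 6 (week 19) |

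**Effect on the 2-of-14 rule (scenario).** Let p be the true response rate and f the assumed share of responders who still qualify under the literal rule. The protocol gives no value for f. With q = p × f, P(at least 2 of 14) = 1 − (1 − q)^14 − 14q(1 − q)^13.

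| f | p = 20% | p = 30% |
| --- | --- | --- |
| 1 | 0.802 | 0.953 |
| 0.75 | 0.643 | 0.857 |
| 0.50 | 0.415 | 0.643 |
| 0.25 | 0.153 | 0.283 |

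**The case against.** Four objections deserve an answer.

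1. The rule may be meant as sustained response over at least 8 weeks, which is workable and confirms at week 25. That reading is plausible, but the text asks for two consecutive evaluations and does not mention a longer run of scans. It would also ask for 12 weeks of response where Section 11.33 plans a check at 6. The objection limits the harm but leaves two readings with different counts.
2. A stricter durability requirement is conservative, and Section 16.3 ties its 20% benchmark to no confirmation interval. This stands. It is therefore not shown that a shorter interval is the true definition or that the response rate is biased by a known amount. What is shown is that the rule and the calendar do not fit.
3. Section 16.6 treats all results as exploratory. That lowers the stakes, but 2 of 14 is still the stated criterion for further study.
4. A statistical analysis plan might settle the matter. That does not apply here: the protocol states a figure that conflicts with its own schedule, which is different from leaving a detail open.

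A reader might infer that no response at all can be confirmed before week 46. The documents do not support that. Scans follow cycle ends, and Section 8.2 allows pembrolizumab to be held, in many rows with up to 12 weeks for resolution. If a hold delays a cycle, a gap could pass 56 days earlier. Such a patient could then qualify by chance while a patient on schedule could not, which is a further oddity of the rule.

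**Conclusion.** The conflict stands, and it lies in the primary endpoint. Through Cycle 12, consecutive on-schedule scans are 42 days apart (36 to 48 with windows) against 56 required. The first scheduled pair that can qualify completes at about week 46, or about week 55 for a response first seen at Cycle 12. These results rest only on the protocol's cycle lengths, windows and scan list, and no other section resolves them.

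The effect on the response count is real but cannot be sized from the protocol. The probabilities above are scenarios under the literal reading, driven by an assumed f. A reader might go further and use the 26% response rate and 22-week median PFS in Section 1.2 to estimate the loss. At p = 26%, the chance of at least 2 of 14 would fall from 0.91 to 0.79 (f = 0.75) or 0.56 (f = 0.50). The documents do not support that as an estimate:

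- The PFS figure covers all patients, not responders, so it does not give f.
- Both figures come from pembrolizumab alone, in a study whose title in the reference list describes ipilimumab-refractory disease. Section 16.1 describes this population as ipilimumab-naïve in the metastatic setting, and Section 3.3 admits patients previously treated with anti-PD-1 or anti-PD-L1 therapy.
- Section 1.2 calls the responses durable, which argues against assuming a heavy loss of responders.

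**What to change.** In both places in Section 16.6, bring the interval into line with Sections 4, 11.1 and 11.33: require CR or PR on two consecutive scheduled evaluations about 6 weeks apart, with a stated tolerance for the visit window. The tolerance is needed because a two-cycle gap can be as short as 36 days, so a strict 6-week minimum would fail some on-schedule pairs. The wording should also count the 6-week follow-up scan of Section 11.33 and the 9-week pairs after Cycle 12. Six weeks is the interval the protocol already uses for the follow-up scan and for confirming progression. A shorter one, such as 4 weeks, has no basis in its response rules.

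No scans are added, and neither the 14 patients nor the 2-of-14 rule changes. The cost is that a primary response definition is altered in an open-label cohort already under way: Section 16.4 counts 6 of the 14 as enrolled at the maximum tolerated dose by Amendment 6. Record the reason for the change, and report the response count under the 8-week rule, read literally, beside the revised one.
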